### Clinical Data Collection

#### Acquisition of MR Images

Brain MR images will be acquired using 3.0-T GE scanners with 8-channel head coils at baseline. All participants will be scanned during natural sleep, as their sleep times will be adjusted based on the experimental schedule, and earplugs will be used to reduce the scanning noise from the MRI chamber. In cases where the child cannot fall asleep to comply with the MRI examination, sedation will be administered after obtaining parental or guardian consent. The potential risks of sedation will be fully explained to the parents or guardians. Each subject’s vital signs will be monitored closely, and head motion will be limited by the placement of foam padding around the child’s head during the MRI examination. Three sequences will be acquired: 3-dimensional fast spoiled gradient-recalled echo (3D-FSPGR) T_1_-weighted imaging (T_1_WI), T_2_-fluid attenuated inversion recovery (T_2_-FLAIR) imaging and diffusion tensor imaging (DTI). Image acquisition parameters of 3D-FSPGR, T1WI, T2-FLAIR, and DTI will be held consistent across sites to reduce the variability of imaging data. The detail scan parameters of the MRI sequences are shown in Table 2.

**TABLE 2 T2:** Scan parameters of the MRI sequences.

Variable	T_2_-FLAIR	3D-FSPGR T_1_WI	DTI
Repetition time (ms)	7500	7.8	12500
Echo time (ms)	145	3.0	86.8
Number of diffusion gradient directions	NA	NA	64
*b* values (s/mm^2^)	NA	NA	0,1000
Slice thickness (mm)	3	1.0	2.5
Gap (mm)	1.5	0	0
Field of view (mm^2^)	240 × 240	256 × 256	240 × 240
Matrix size	256 × 256	256 × 256	256 × 256

*T_2_-FLAIR, T_2_-fluid attenuated inversion recovery; 3D-FSPGR T_1_WI, 3-dimensional fast spoiled gradient-recalled echo T_1_ weighted imaging; DTI, diffusion tensor imaging; NA, not available.*

#### Lesion Masks

Periventricular white matter lesions will be characterized as areas of T_2_ hyperintensity with or without cystic degeneration. The lesion masks will be manually delineated on T_2_-FLAIR images using ITK-snap software (Yushkevich et al., 2006) by two neuroradiologists. Intrarater and interrater reliability in lesion segmentation will be evaluated using the Dice κ consistency test (Guo et al., 2017). If there is an evident discrepancy, a third neuroradiologist will be invited to make the final decision. Then, the T_2_-FLAIR image will be coregistered to the T_1_ image, and these parameters will be used to reslice the lesion mask into the native T_1_ space. The resliced lesion masks will be binarized using a 50% probability threshold. The alignment between the resliced lesion masks and the lesions in native T_2_ space will be visually inspected by two experienced neuroradiologists by comparing the overlay of the resliced lesion mask to the patient’s native T_1_ image to the overlay of the original lesion mask on the patient’s native T_2_-FLAIR image. Cases of misalignment will be manually corrected directly in the normalized lesion mask using ITK-snap software.

#### Lesion (Voxel)-Based Analysis

Two complimentary approaches (lesion- and connectome-based) will be used to characterize brain damage. Both of them will use a brain atlas developed by Oishi et al. (2011) to divide the brain into 122 regions to reduce the feature dimensions. For lesion-based and connectome-based analysis, the brain atlas containing the parcelation information will be aligned to each individual’s native T_1_ images. First, the T_1_ target image of patients will be created by using a groupwise template creation method (Li et al., 2016). Then the patients T_1_ target image will be registered to the infant T_1_WI template provided by Oishi et al. (2011) in the standard space. Subsequently, these deformation parameters will be inverted and applied on the brain atlas in the standard space to obtain the brain atlas in the local patient target space and individual’s native T_1_ space. The unified segmentation function of SPM12 (Ashburner and Friston, 2005) will be used to obtain the probabilistic gray and white matter maps from T_1_ images. These probabilistic gray maps (in native T_1_ space) will be further divided into regions of interest (ROIs) corresponding to the brain atlas. Then, lesion-based analysis will be computed as the proportion of lesioned voxels per ROI (each cortical and subcortical gray matter region corresponding to the brain atlas).

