#### Inclusion Criteria

Children meeting the following criteria will be considered for enrollment in this study: (I) confirmed diagnosis of BCP by pediatric neurologists (Novak et al., 2017), (II) age 6 months to 2 years at the time of recruitment, (III) PWMLs as described on the MRI imaging report, and (IV) willingness by participants and parents to participate in the study.

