### Models for Predicting Communication Impairment

#### Preselection of Predictive Features

Since the number of streamlines between two cortical regions is averaged, the connectivity matrix is symmetrical with respect to the diagonal, and only the lower triangular matrix will be used for further analyses. For both lesion-based and connectome-based analyses, the feature set will include hundreds to thousands of feature vectors, and such high-dimensional data can cause the “curse of dimensionality.” To reduce the number of potential features introduced into the predictive model, a preselection procedure will be performed to exclude noisy or uninformative predictors from being fed into the prediction model, which can reduce the chance of model overfitting. First, for lesion-based analyses, only gray matter regions that are lesioned in more than 10% of the patients will be entered into the analysis. Second, for the links in the connectome matrix-based analyses, only those that are present in more than 75% of the patients will be entered into the analysis. After the above steps, each subject will have three feature sets: the lesion feature set, connectome feature set, and combination feature set.

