**FIGURE 2 F2:**
[figure not shown]
Data processing and analysis workflow. **(A)** First, the lesion will be manually defined on T_2_-FLAIR images. **(B)** Two complementary methods, one based on lesions and the other on the connectome, will be used to characterize brain damage. To compute lesion-based damage (top row), the brain atlas and each individual’s lesion mask will be aligned with each individual’s native T_1_ space. The gray matter regions will be divided into regions of interest (ROIs) according to the atlas. Then, lesion-based damage will be computed as the proportion of lesioned voxels per ROI based on the lesion mask. Connectome-based damage (bottom row) will be computed as the number of diffusion tensor imaging (DTI) tracts that connect each pair of ROIs (tractography for reconstructing tracts will be performed guided by the white matter probabilistic map). **(C)** For each individual, three feature sets (lesion features, connectome features, and combination features) will be generated from the corresponding features after feature selection. **(D)** For each feature set, a “training cohort” will be used to build an optimal model based on a 10-fold cross-validation, and the prediction performance of the optimal model will be tested with the “test cohort” using ROC curve. **(E)** Then, three optimal models will be generated based on different feature sets (the lesion feature set for voxel model, the connectome feature set for connectome model, and the combination feature set for combination model). The prediction performance of each model will be compared, and the best-performing model will be selected.

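### Lesion load is computed only in gray-matter regions although the masks are periventricular white-matter lesions, so the lesion features omit the white-matter extent of the injury

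*Protocol article*

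**What the plan says.** All places are in the protocol article.

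- *Inclusion Criteria* requires "PWMLs as described on the MRI imaging report".
- *Lesion Masks* defines one lesion type for delineation: "Periventricular white matter lesions will be characterized as areas of T_2_ hyperintensity with or without cystic degeneration".
- *Lesion (Voxel)-Based Analysis* obtains gray- and white-matter probability maps from the T1 image, but cuts the regions of interest (ROIs) from the gray map: "These probabilistic gray maps (in native T_1_ space) will be further divided into regions of interest (ROIs) corresponding to the brain atlas". The lesion feature is then the "proportion of lesioned voxels per ROI (each cortical and subcortical gray matter region corresponding to the brain atlas".
- The *Figure 2* legend repeats this: "The gray matter regions will be divided into regions of interest (ROIs) according to the atlas".
- *Preselection of Predictive Features* filters on the same basis: "only gray matter regions that are lesioned in more than 10% of the patients will be entered into the analysis".
- *Connectome-Based Analysis* gives the white-matter map its only stated analytic use, as the waypoint mask for tractography.

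No section computes lesion load in a white-matter region or says how far the masks are expected to overlap gray matter.

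**The concern.** The case for predicting communication from MRI rests largely on PWMLs. The *Introduction* and *Participants* cite studies in which more severe PWMLs went with worse communication, and this is one reason the population was restricted. The *Introduction* also lists the left posterior internal capsule, a white-matter structure, among the language-pathway regions whose damage went with poorer communication. A gray-matter ROI list cannot register lesion load there.

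Three things are affected:

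1. The lesion model, and the lesion part of the combination model, are built without the white-matter extent of the lesion.
2. *Development and Validation of Prediction Models* tests whether the multimodality model is more accurate than any single-modality model. A gain over the lesion model could partly reflect how the lesion feature was defined.
3. The *Discussion* expects the voxel-based analysis to show which regions go with impairment. As defined, it cannot point to a white-matter region.

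**Working it through.** **Step 1. Follow one lesioned voxel through the pipeline.**

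| Stage | Section | Tissue |
|---|---|---|
| Eligibility | Inclusion Criteria | White-matter lesion required |
| Mask | Lesion Masks | White-matter lesion |
| ROI | Lesion (Voxel)-Based Analysis; Figure 2 legend | Gray matter, cortical and subcortical |
| Feature | Lesion (Voxel)-Based Analysis | Share of gray ROI voxels inside the mask |
| 10% filter | Preselection of Predictive Features | Gray-matter regions |
| White-matter map | Connectome-Based Analysis | Tractography only |

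A mask voxel in white matter belongs to no ROI and adds nothing to any lesion feature. Three places agree on gray matter, so this is not a slip in one sentence.

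**Step 2. Where non-zero features can come from.** Two sources remain: true extension into adjacent deep gray matter, and overlap at tissue boundaries through partial volume, reslicing or segmentation error. Table 2 makes the second plausible. FLAIR slices are 3 mm with a 1.5 mm gap, so spacing is 3 + 1.5 = 4.5 mm and 1.5/4.5 = one third of the through-plane extent is unsampled. The T1 image has 1.0 mm slices and no gap.

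**Step 3. The plan's own sample size, used here only as a denominator.** With f² = 0.10, 6 predictors and α = 0.05, the noncentral F test (λ = f²N, df 6 and N − 7) gives power 0.7977 at N = 142 and 0.8011 at N = 143. The stated 143 reproduces. Dropout gives 143/0.8 = 178.75, against 178 stated, a rounding difference of no consequence.

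**Step 4. What the 10% filter does.** More than 10% means at least 15 of 143 children (0.10 × 143 = 14.3) or 18 of 178 (17.8). Let p be the chance that a child's mask touches a given gray ROI at all. The documents do not give p, so the values below are assumptions. The chance that the ROI passes is the binomial tail P(X ≥ 15) or P(X ≥ 18).

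| Assumed p | Passes, n = 143 | Passes, n = 178 |
|---|---|---|
| 5% | 0.006 | 0.004 |
| 7.5% | 0.12 | 0.12 |
| 10% | 0.46 | 0.52 |
| 15% | 0.95 | 0.98 |
| 20% | 0.999 | 0.9999 |

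ROIs seldom touched by the mask drop out almost surely. ROIs touched in 15% or more of children almost surely stay, even on a single voxel each, because the filter as written sets no minimum overlap. The table shows how the rule behaves. It does not estimate how many ROIs will survive.

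**The case against.** **The lesion set need not be empty.** A reader might infer that it will be nearly empty, or made up of misregistration. The documents do not support that. They report no overlap figure. Subcortical gray matter is already in the ROI list, the *Introduction* cites lesions of the thalamus, caudate and lenticular nuclei in children with CP, and coexisting deep-gray injury is not an exclusion. Under *Lesion Masks*, two neuroradiologists inspect mask alignment and errors are corrected by hand, although that check covers the mask and not the atlas or the gray-matter map. Step 4 shows that ROIs can pass easily if touched often enough. This part of the objection stands.

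**White-matter injury is covered elsewhere.** Streamlines are tracked through the white-matter map, so the connectome features reflect such injury indirectly and enter both the connectome and combination models. The multimodality comparison also includes the connectome model. Gray-matter ROIs suit the secondary aim on cortical regions. This limits the damage but does not repair the lesion features: the connectome is not computed from the lesion mask, and lesion load in white matter remains unmeasured.

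**The link-presence rule.** A reader might extend the point to the connectome filter, under which "only those that are present in more than 75% of the patients will be entered into the analysis", and infer that it deletes the links most damaged by injury. If a link is present in every unimpaired child and wholly lost in a share q of impaired children, it is dropped once prevalence × q reaches 0.25. That means q of 0.25/0.47 = 53% or 0.25/0.78 = 32% at the two prevalences quoted. This counts only complete loss, whereas the feature is a graded streamline weight that can fall without vanishing. The documents do not show that such losses occur. Loosening the rule would also trade against noise: up to 122 × 121/2 = 7,381 links would face about 0.75 × 143 = 107 evaluable training children. No change to that rule is proposed.

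**Conclusion.** The mismatch is real and consistently stated. Followed exactly, the plan measures lesion load only in gray matter while its masks are white-matter lesions. Two of the three models are affected in their lesion component, and the combination-versus-lesion comparison may partly reflect the feature definition.

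The loss of predictive accuracy cannot be quantified, because the overlap of the masks with gray matter is not given. The conclusion rests on the masks being drawn as *Lesion Masks* defines them, and on the ROIs being cut from the gray map as written. It does not show that the lesion set will be empty, that misregistration explains what remains, or that the primary aim fails.

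**What to change.** Before features are extracted, amend *Lesion (Voxel)-Based Analysis*, *Preselection of Predictive Features* and the *Figure 2* legend as follows:

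- compute the share of lesioned voxels in white-matter parcels as well, using the aligned atlas and the white-matter probability map already produced;
- keep the existing cortical and subcortical gray-matter ROIs;
- apply the 10% rule to all of these regions.

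The article does not say whether the atlas's 122 regions include white-matter labels. If they do not, the white-matter parcels must be specified.

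The cost is a longer ROI list in an existing pipeline and a modest increase in candidate lesion features entering the univariate filter. No new scans, masks or readers are needed.

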#### Connectome-Based Analysis

The structural brain connectome will be computed as the number of white matter streamlines that connect each pair of cortical and subcortical gray matter regions, and probabilistic tractography will be performed in individual’s diffusion space to construct the connectome. Thus, the tissue maps (including the ROI-segmented gray matte map) will be registered into an individual’s diffusion-weighted imaging (DWI) space. First, since tissue contrast is comparable between B0 and T_2_ images, the registered T_2_-FLAIR image (coregistered into the native T_1_ image) will be linearly normalized into the mean B0 image from the diffusion MRI sequence using the FMRIB Software Library (FSL) Linear Image Registration Tool (Greve and Fischl, 2009) (correlation ratio cost function, affine registration with 12 parameters and nearest neighbor interpolation). The transformation matrices will then be used to register the probabilistic maps of white and gray matter, and segmented cortical ROIs in native T_1_ space into DWI space.

Probabilistic tractography will be applied to evaluate the structural connectivity of pairwise cortical regions, which will be separately defined according to the brain atlas. Structural connectivity will be obtained by the probabilistic method of the FMRIB Diffusion Toolbox (FDT) (Behrens et al., 2007) for fiber tracking. FDT BEDPOST will be used to build the default distributions of diffusion parameters at each voxel. Probabilistic tractography will be obtained using FDT’s probtrackx (Behrens et al., 2007) (parameters: 5,000 individual streamlines drawn through the probability distributions on principle fiber direction, step length of 0.5 mm, 200 maximum steps, curvature threshold set at 0.2, and distance correction) since probabilistic tractography is theoretically capable of accommodating intravoxel fiber crossings. The probabilistic white matter map will be used as the waypoint mask (Yourganov et al., 2016; Gleichgerrcht et al., 2017). The cortical ROIs (corresponding to the brain atlas) in diffusion space will be used as seed regions for tractography. For each subject, the connectivity between cortical ROIs i and j will be calculated, defined as the number of streamlines arriving at j when i is seeded, averaged with the number of streamlines arriving at i when j is seeded. The calculation of the streamlines will be corrected based on the distance traveled (“distance correction” built into probtrackx). In addition, the number of streamlines between ROIs i and j will be divided by the sum of the volume of the two regions to eliminate the effects of the unequal sizes of the different cortical regions. These steps will be repeated iteratively to ensure that all cortical ROIs are used as seed regions. Once all iterations are completed, a connectivity matrix A will be constructed, where each entry Aij represents the connection weight between cortical ROIs i and j.

#### Harmonization

Multisite imaging studies are prone to technical variability across scans, including differences between the manufacturers, heterogeneity in the protocol and variations in the scanning parameters. Such unwanted variation can hinder the detection of important features and/or cause spurious findings. There is a need to remove the bias and non-biological variance caused by unwanted site effects. In this study, we will use ComBat (Fortin et al., 2017, 2018), a method that adjusts the mean value and variance between different groups by combining an empirical Bayes framework and the location/scale model, to harmonize the data. Studies have shown that the ComBat method performs well in preserving biological variability and removing the unwanted variation introduced by site for harmonizing the 3DT_1_ imaging (Fortin et al., 2018) and DTI (Fortin et al., 2017).

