**Methods:**

A multicenter prospective cohort study will be conducted in four Chinese hospitals. A total of 178 children with BCP will undergo advanced brain magnetic resonance imaging (MRI) at baseline (corrected age, before the age of 2 years). At school entry, communication performance will be assessed by a communication function classification system (CFCS). Three-quarters of children with BCP will be allocated as a training cohort, whereas the remaining children will be allocated as a test cohort. Multivariate lesion- and connectome-based approaches, which have shown good predictive ability of language performance in stroke patients, will be applied to extract features from MR images for each child with BCP. Multiple machine learning models using extracted features to predict communication impairment for each child with BCP will be constructed using data from the training cohort and externally validated using data from the test cohort. Prediction accuracy across models in the test cohort will be statistically compared.

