**Discussion:**

The findings of the study may lead to the development of several translational tools that can individually predict communication impairment in children newly diagnosed with BCP to ensure that these children receive early, targeted therapeutic intervention before they begin school.

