Multivariate lesion- and connectome-based approaches (Gleichgerrcht et al., 2017) are emerging techniques that provide an objective and quantifiable way to statistically evaluate the relationship between whole-brain structure connections and behavioral function. Notably, a prediction model constructed from this approach had high efficacy in the prediction of language deficits in post-stroke patients (Yourganov et al., 2016) and motor outcomes in neonates with arterial ischemic stroke (Al Harrach et al., 2021). Therefore, this study aims to develop individual prediction models based on multivariate lesion- and connectome-based approaches at an early age to predict communication ability in children with CP by the time they enter school. Among all types of CP, bilateral cerebral palsy (BCP) is the most common subtype, comprising 64.7% of all cases (Colver et al., 2014). Furthermore, different neuroimaging findings have revealed different patterns of insult to the brain in CP; recent research has noted that white matter lesions are the most common findings in imaging, accounting for 49.1% of all cases, and the severity of PWMLs has been verified to be linked with communication performance in children with CP (Geytenbeek et al., 2015; Coleman et al., 2016; Choi et al., 2017). Thus, we will also limit study participants to those with BCP and PWMLs (the most common subtype and neuroimaging finding in children with CP) to reduce the heterogeneity within the study population to improve the accuracy of prediction models. The results of this study may lead to the development of several translational tools that can be used to make individualized predictions of communication impairments in children newly diagnosed with BCP and PWMLs to ensure that these children receive early, targeted therapeutic intervention before they begin school.

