Images from four sites (four hospitals) will be randomly partitioned into four equal portions. Approximately three-quarters of these images will be used as a “training cohort,” and the remaining one-quarter of these images will be used as a “test cohort.” In the “training cohort,” the proportion of lesioned voxels in the ROI and the links of the connectome matrix that are not shown difference between absence of communication impairment group and communication impairment group will be excluded, where the significance level is defined as *P* < 0.05 without multiple comparison correction in the two-sample test. The selected features will be used to define models predicting presence or absence of communication impairment in children with BCP. For each prediction model, 10-fold cross-validation (CV) will be used to evaluate the performance. This means that the “training cohort” will be divided into a training (nine folds) and a validation dataset (one fold), leaving 9 of 10 participants in the training dataset and the remaining participants in the testing dataset. For the training cohort, the various hyperparameters within each algorithm will be used to determine the prediction model. Then, the model will be applied to the validation dataset to predict children with the presence or absence of communication impairment (predicted label). The same procedure will be repeated with each of the one-fold participants or the left-out participants in the leave-one-out procedure, serving as the validation dataset for 10 iterations. Thus, each subject will receive a predicted label, and the accuracy of predictive model will be evaluate by comparing predicted labels to true labels of BCP children. The CV step will be repeated 100 times with random cohort designation to select the model with the best prediction accuracy. The whole “training cohort” will be reused in its entirety to retrain the model based on the classification algorithm and hyperparameters of the prior selected model. Then, the retrained model will be used to evaluate the “test cohort,” and the communication performance of every subject of the “test cohort” will be predicted by the model. The final accuracy of the prediction model will be defined by comparing predicted labels to true labels of BCP children in the “test cohort,” The Receiver Operating Characteristic (ROC) curve and the area under curve (AUC) will be calculated to evaluate the predictive ability of built models. A two-sided Hotelling-Williams test (Steiger, 1980) will be used to determine whether the multimodality prediction model is more accurate than any of the single-modality prediction models. *P* values < 0.05 will be considered indicative of statistically significant differences across models. Given the possible effects of age on imaging measures, the “test cohort” will be divided into three groups: younger (6–12 months), middle-aged (12–18 months), and elderly (18–24 months years), according to their age at MRI scan. The optimal model will be applied to all subgroups to exam whether the prediction accuracy changes with age at MRI scan.

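### Every planned accuracy and AUC describes site-harmonized children at the four study hospitals; no child from another hospital is provided for or tested, yet the test is called external validation and the claims are not limited to these sites

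*Protocol article*

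**What the plan says.** Five parts of the Protocol article bear on this.

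- **Harmonization.** The stated reason is that "There is a need to remove the bias and non-biological variance caused by unwanted site effects". The tool is ComBat, "a method that adjusts the mean value and variance between different groups by combining an empirical Bayes framework and the location/scale model". The main Discussion repeats that ComBat will be used to remove site effects.
- **Acquisition of MR Images.** Baseline scans use 3.0-T GE scanners with 8-channel head coils, and sequence parameters "will be held consistent across sites to reduce the variability of imaging data".
- **Development and Validation of Prediction Models** (text after Figure 2). "Images from four sites (four hospitals) will be randomly partitioned into four equal portions"; about three quarters form the training cohort and one quarter the test cohort. Final accuracy, ROC curve and AUC come from the test cohort.
- **Abstract, Methods.** The models will be "externally validated using data from the test cohort".
- **Claims and limits.** The Abstract's Discussion speaks of "translational tools that can individually predict communication impairment in children newly diagnosed with BCP" and the Introduction of "translational tools that can be used to make individualized predictions of communication impairments in children newly diagnosed with BCP and PWMLs". Both sentences say that the findings may lead to such tools. The main Discussion says more directly that the model can inform the timing of intervention and decisions. Its closing limitation restricts generalizability by CP subtype and by neuroimaging finding only.

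**The concern.** A location/scale correction needs an estimate of location and scale for the site a child comes from. In the planned split, each test child comes from a hospital that also contributes training children, so such an estimate is available. One newly diagnosed child at a hospital outside the study brings none, and the article does not say what would be done. The planned test therefore cannot show how the model performs there.

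What is at stake is the reach of the conclusion. A reader told that a model for individual prediction was externally validated will take the reported accuracy and AUC to apply at other hospitals. The design supports them only for new children at the four study hospitals, processed with those hospitals' site parameters.

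**Working it through.** **1. The passages side by side.** The correction is defined by site (Harmonization). The test cohort is a random quarter of the pooled children from the same sites (Development and Validation of Prediction Models). No hospital is held out. So every test result is a within-site result on harmonized inputs. That conflicts with the word external in the Abstract, and nothing in the limitations corrects it.

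**2. The plan's own reasoning.** Scanner make, field strength, coil and parameters are matched across sites, and the plan still holds that site effects must be removed. If correction is needed among matched scanners, it cannot be presumed needless at a hospital whose scanner may not match. If matching makes it needless, a model on unharmonized features would lose little. The planned analyses cannot tell these cases apart.

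**3. Numbers available.** The plan's sample size reproduces: for a multiple regression F test with f² = 0.10, 6 predictors and α = 0.05, the smallest N with power of at least 0.80 is 143 (power 0.801). The dropout step is 143/0.80 = 178.75, against 178 stated. For the 143 evaluable children, assuming equal recruitment:

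- test cohort: 143/4 = 35.75, about 36, or about 9 per hospital (143/16 = 8.9);
- training cohort: about 107, or about 27 per hospital (143 × 3/16 = 26.8);
- one hospital held out: about 36 test children and about 107 for training, the same sizes as the random split.

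If accuracy is 0.75 (assumed), the 95% half-width with 36 children is 1.96 × √(0.75 × 0.25/36) = 0.14. Pooled over four hold-outs (143 predictions) it is 1.96 × √(0.75 × 0.25/143) = 0.07. This ignores variation between hospitals, which four hospitals estimate poorly.

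**4. How large the loss could be.** The documents give no site-effect size. Two illustrations on assumed inputs show the range.

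*(a) Fixed cut-off.* Take an equal-variance normal score with AUC 0.80 and a midpoint cut-off. Then d = √2 × z(0.80) = 1.190. With an uncorrected shift of s SD of the score, sensitivity = Φ(d/2 + s) and specificity = Φ(d/2 − s). Accuracy is for equal class sizes.

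| s | sensitivity | specificity | accuracy |
|---|---|---|---|
| 0 | 0.724 | 0.724 | 0.724 |
| 0.25 | 0.801 | 0.635 | 0.718 |
| 0.5 | 0.863 | 0.538 | 0.701 |
| 1.0 | 0.945 | 0.343 | 0.644 |

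A uniform shift leaves AUC within one hospital unchanged; the damage is to the yes/no call.

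*(b) Simulation.* Assumed: 143 children, four hospitals, random 3/4 to 1/4 split, 30 features of which 8 are informative at 0.6 SD, half the children impaired, ComBat fitted in training, a regularized linear classifier and 300 replicates. Site shifts and scale differences were drawn per feature. Children from unseen hospitals were standardized with the pooled mean and SD only, and their AUC was computed across six such hospitals together.

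| site shift SD (log-scale SD) | AUC same-site | AUC unseen | accuracy same-site | accuracy unseen |
|---|---|---|---|---|
| 0 (0) | 0.83 | 0.83 | 0.75 | 0.75 |
| 0.25 (0.10) | 0.83 | 0.83 | 0.74 | 0.75 |
| 0.5 (0.15) | 0.83 | 0.81 | 0.75 | 0.73 |
| 1.0 (0.20) | 0.83 | 0.77 | 0.75 | 0.68 |
| 1.5 (0.30) | 0.83 | 0.73 | 0.75 | 0.64 |

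The same-site columns barely move. The planned test would look the same whether the loss elsewhere is nil or large.

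**The case against.** ComBat is a reasonable choice for a four-site imaging study, and the Harmonization section states nothing false about it. The Abstract and Introduction are hedged: the findings may lead to tools, and no sentence names use at a non-study hospital. How a new site would be handled is a detail that an article may leave to a fuller document. With matched scanners the site effect may be small, and at 0.25 SD both illustrations show almost no loss. Every input to those illustrations is assumed.

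Much of this stands. The hedge softens the conflict, and the size of any loss is not shown. What it does not answer is the conflict among things the article does state: a random split within the same sites called external, claims not restricted by hospital, and a limitations paragraph that omits hospital and scanner.

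A reader might infer more: that features are corrected with each hospital's own mean and variance, so the model cannot be used as an individual tool at all. The documents do not support that. The empirical Bayes step shrinks the site estimates. Values frozen from the training cohort would serve a single new child at any of the four hospitals, and another hospital could estimate its own from a local reference sample.

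A reader might also think that unharmonized models on the same random split would give the figure for a new hospital. They would not: those models are trained and tested on the same four hospitals, so the result is again within-site. If impairment prevalence differs by hospital, such a model could even gain from site signal.

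**Conclusion.** The point holds in a limited form. The planned accuracy and AUC describe site-harmonized features at hospitals that also supplied training data. The plan gives no route for a child from another hospital and tests none, so the random-split result does not establish performance there and should not be called external validation. This does not make the model unusable, and it does not undermine the primary aim within the four hospitals.

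The size of any loss elsewhere is unknown and may be negligible or large. The illustrated range, unseen-hospital AUC from 0.83 down to 0.73 against 0.83 at the same sites, rests entirely on assumed site effects and assumed signal. The argument from the passages does not depend on those figures.

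**What to change.** 1. **Harmonization, and Development and Validation of Prediction Models:** state that ComBat parameters are estimated in the training cohort only, and within the training folds during cross-validation, then applied as frozen values to the held-out children. The article does not say whether ComBat is fitted before or after the split; this settles it and makes the score computable for a single new child at a study hospital.

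2. **Same section:** add a leave-one-hospital-out analysis on the existing data, with and without harmonization, repeating feature screening and tuning within the three remaining hospitals. In the harmonized version, score the held-out hospital's children without site parameters (for example with the pooled mean and SD). This is the estimate for a hospital without site reference data.

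3. **Wording:** in the Abstract's Methods, replace external validation with internal (random-split) validation. In the Abstract's Discussion, the Introduction, the main Discussion and its limitations, state that performance outside the four hospitals is not established by the random-split test.

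The cost is extra model runs on data already collected and a few sentences. The downside is that each held-out hospital has about 36 evaluable children if recruitment is equal, and some have fewer if it is not. The result will be imprecise and may be less favourable than the random-split figure.
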